## Abstract

**Background:**

Diabetes mellitus may be present in patients with cystic fibrosis starting in the second decade of life. The prevalence increases rapidly with increasing age. As life-expectancy increases in cystic fibrosis, cystic fibrosis related diabetes will be diagnosed more frequently in the future.

Up to date, no data are available to answer the question if cystic fibrosis related diabetes should always initially be treated by insulin therapy. Missing data regarding oral antidiabetic treatment of newly diagnosed cystic fibrosis related diabetes are an important reason to recommend insulin treatment. Several centres report the successful management of cystic fibrosis related diabetes using oral anti-diabetic drugs at least for some years. Oral therapies would be less invasive for a patient group which is highly traumatized by a very demanding therapy. Based on an initiative of the German Mukoviszidosis-Foundation, the present study tries to answer the question, whether oral therapy with repaglinide is as effective as insulin therapy in cystic fibrosis patients with early diagnosed diabetes mellitus.

**Methods/Design:**

In all cystic fibrosis patients with an age of 10 years or older, an oral glucose tolerance test is recommended. The result of this test is classified according to the WHO cut off values. It is required to have two diabetes positive oral glucose tolerance tests for the diagnosis of diabetes mellitus.

This study is a multi-national, multicentre, open labelled, randomized and prospective controlled parallel group’s trial, with 24 months treatment.

The primary objective of this trial is to compare the glycaemic control of oral therapy with Repaglinide with insulin injections in patients with cystic fibrosis related diabetes after 2 years of treatment.

The trial should include 74 subjects showing cystic fibrosis related diabetes newly diagnosed by oral glucose tolerance test during annual screening for cystic fibrosis related diabetes.

Patients are randomised by central fax randomisation.

Primary endpoint is mean HbA1c after 24 months of treatment. Secondary endpoints are change in FEV1% predicted and change in BMI-Z-score.

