### Power calculation/analysis

Which number of patients was necessary to show a significant difference between therapy strains of 80% power on the one hand and p <0.05 on the other? Retrospective HbA1c data from a database of the CF centre at Medical School Hannover were used. Measurements of n = 132 HbA1c within the first two years after diabetes diagnosis of n = 44 patients older than 10 years at the date of diagnosis resulted in an average value of HbA1c = 5.6 ± 1.5 (average value ± SD). Within a similar group (older than 10 years) but without diabetes n = 763 measurements yielded an HbA1c of 4.6 ± 0.68 (average value ± SD). A difference of 1 (which is in the range of individual variations during treatment especially in youngsters and young adults) between therapy groups was considered relevant [12]. Calculation with *n Query®* of necessary patients for each group was done with these parameters: Two group *t*-test of equal means (equal n’s) 1; Test significance level, α 0,050; 2 sided test; Group 1 mean, μ_1_ 5,600; Group 2 mean, μ_2_ 4,760; Difference in means, μ_1_ - μ_2_ 1,000; Common standard deviation, σ 1,500; Effect size, δ = |μ_1_ - μ_2_|/σ 0,667; Power 80%. Based on the above assumptions the number of patients in each group was calculated as n = 37. Over a treatment time of 2 years, about 30% of patients were assumed to drop out of the study. Therefore, n = 111 patients have been necessary at the beginning of the study to ensure a number of n = 74 remaining patients at the end of the study.

For analysis, the differences of primary parameter HbA1c repeated measures-ANOVA will be applied. The one-sided zero hypothesis (Repaglinide is not worse than insulin) will be dismissed if a p value under 0.05 occurs. The two therapy groups will be compared concerning secondary parameters statistically using the fisher exact test (comparison of discrete events), the Wilcoxon (non-parametrically distributed parameters) and the *t*-test (parametrically distributed parameters). For comparison of drop-outs between the treatment stains a Cox proportional-hazard-ratio model will be applied.

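### The abstract gives 74 as the number of subjects to include, but the power section gives 74 as the number remaining at the end and 111 as the number needed at entry

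*Protocol article*

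**What the plan says.** The Methods/Design part of the abstract says: "The trial should include 74 subjects showing cystic fibrosis related diabetes newly diagnosed by oral glucose tolerance test". It does not mention drop-out.

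The section Power calculation/analysis builds the number in two steps. First, "Based on the above assumptions the number of patients in each group was calculated as n = 37", which makes 74 in total. Second, it allows for loss: "Over a treatment time of 2 years, about 30% of patients were assumed to drop out of the study". It then concludes that "n = 111 patients have been necessary at the beginning of the study to ensure a number of n = 74 remaining patients".

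Two other sections bear on the point. Randomization asks that every randomised patient be followed for at least two years and be part of an intention-to-treat analysis. Trial status reports 1093 patients screened, 145 diagnosed, and the dates on which the first and last patients entered (March 2002 and December 2009). It does not report how many were randomised.

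**The concern.** The same figure has two meanings. In the abstract, 74 is the number to include; in the power section it is the number that must be left after losses, and the entry number is 111. Trial status uses the word included for patients entering the trial, so the natural reading of the abstract is an entry number.

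A reader who relies on the abstract would regard 74 randomised patients as full recruitment. By the power section, that is two thirds of what is needed (74/111 = 0.667). The trial asks whether repaglinide is as effective as insulin. If its power were well below the stated 80%, a non-significant result could too easily be taken as showing that the two treatments perform alike.

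**Working it through.** **Inputs, all from Power calculation/analysis:** two-group t-test with equal group sizes, two-sided; "Test significance level, α 0,050"; "Difference in means, μ_1_ - μ_2_ 1,000"; common SD 1.5; power 80%; drop-out about 30%.

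**Step 1. Reproduce the plan's own figure.** Standardised effect = 1.0/1.5 = 0.667. Power comes from the noncentral t distribution with 2n − 2 degrees of freedom and noncentrality 0.667/√(2/n), where n is the number per group.

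- n = 36: power 79.7%
- n = 37: power 80.8%

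The smallest n that reaches 80% is 37, or 74 in total, as stated. So 74 is the number of patients with usable outcome data that the calculation needs.

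**Step 2. Entry number.** To keep N patients after a drop-out proportion d, N/(1 − d) must enter.

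- d = 0.30: 74/0.70 = 105.7, so 106
- d = 1/3: 74/(2/3) = 111

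The printed 111 therefore corresponds to one-third drop-out. Entering 111 and losing 30% leaves 111 × 0.70 = 77.7, about 78. With 38 to 39 per group, power is 81.8% to 82.8%. The rounding is loose but does no harm.

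**Step 3. What follows if 74 is read as the entry number.**

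| Entered | Patients with 24-month HbA1c | Per group | Power | 95% CI half-width |
|---|---|---|---|---|
| 74 | 74 × 0.70 = 51.8, about 52 | 26 | 65.4% | 0.84 |
| 74 | 74 (no loss) | 37 | 80.8% | 0.70 |

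The half-width is t(0.975; 2n − 2) × 1.5 × √(2/n). For n = 26 this is 2.009 × 1.5 × 0.277 = 0.84; for n = 37 it is 1.993 × 1.5 × 0.232 = 0.70 (rounded).

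**Step 4. Dependence on other inputs in the same section.** The figures above use the stated difference of 1.0 and the two-sided test of the sample-size calculation. The printed group means, 5.600 and 4.760, differ by 0.84; that difference would give about 51% power with 26 per group. The same section also describes a one-sided test at 0.05 for the analysis; that would give about 77% with 26 per group and a difference of 1.0. These are separate inconsistencies. They move the power figure but have no bearing on the conflict between 74 and 111.

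**The case against.** The strongest reply is that the power section is unambiguous and is where the plan is set: 74 remaining, 111 at entry. On this view the abstract has merely carried over the wrong one of two numbers, and the trial does not have two recruitment targets. That largely stands. It makes this an error of statement in the abstract and not evidence of a competing design decision. The abstract is still wrong as printed, and it is the most widely read statement of trial size.

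The second reply is that intention-to-treat follow-up would preserve the power. Randomization asks for two years of observation and inclusion in the analysis for every randomised patient, and stopping the assigned therapy need not end HbA1c measurement. With all 74 measured at 24 months, power is 80.8%. This also stands, and it is why the 65% can only be conditional. Against it, the power section enlarges 74 to 111 solely because it treats drop-outs as lost to the comparison, so the 65% follows from the protocol's own assumption.

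The third reply is that the mismatch between 111 and 30% is trivial, because the text says about 30% and 111 is the more cautious number. That is right, and the mismatch is only a note here.

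A reader might go further and infer that the trial recruited only 74 patients and is underpowered. The article does not support this. It does not give the number randomised, and the 145 patients diagnosed are compatible with either 74 or 111 entering.

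**Conclusion.** The inconsistency is real and unresolved in the article: 74 is an entry number in the abstract and an end-of-study number in the power section, where the entry number is 111. The gap is 37 patients, one third of the planned entry.

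The drop from 80% to about 65% power rests on three conditions: 74 was the number that entered, 30% of them dropped out, and those patients gave no 24-month HbA1c. It also takes the difference of 1.0, SD 1.5 and two-sided alpha of 0.05 as stated. If follow-up of the 74 were complete, power would be about 81%. It would therefore be too strong to say that entering 74 necessarily gives 65%, or that only the larger entry number can deliver 80%. The base calculation of 37 per group is correct.

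**What to change.** 1. Align the abstract with the power section: 111 to be randomised so that 74 remain evaluable at 24 months.
2. Report the number actually randomised, the number with a 24-month HbA1c, and the confidence interval achieved for the difference between the groups.
3. If about 74 were randomised, restate the power as about 65% under the stated drop-out assumption, and give the 81% for complete follow-up beside it.
4. As a minor clarification, state the drop-out rate actually used to reach 111 (one third, if that is what was planned). A revised target of 106 is not needed: recruitment closed in December 2009, and the discrepancy errs on the safe side.

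The cost is a text correction and possibly a less favourable statement of power. No further patients are needed. Trial status says that the analysis is still under way, so the correction can be made before the results are interpreted.

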**Discussion:**

There is only one prospective study comparing oral antidiabetic drugs to insulin in the treatment of CFRD without fasting hyperglycaemia. The results regarding BMI after 6 months and 12 months showed an improvement for the insulin treated patients and were inconsistent for those treated with repaglinide. HbA1c and lung function (FEV1%pred) were unchanged for either group. The authors compared the changes -12 months to baseline and baseline to +12 months separately for each group. Therefore a direct comparison of the effect of repaglinide versus insulin on BMI, HbA1c and FEV1%pred was not presented. According to our protocol, we will directly compare treatment effects (HbA1c, BMI, FEV1%pred) in between both groups. The actual Cochrane report regarding “Insulin and oral agents for managing CFRD” stated that further studies are needed to establish whether there is clear benefit for hypoglycemic agents. We expect that the results of our study will help to address this clinical need.

**Trial registration:**

ClinicalTrials.gov Identifier: NCT00662714

## Background

Diabetes mellitus may be present in patients with cystic fibrosis (CF) starting in the second decade of life. The prevalence increases rapidly with increasing age reaching around 30-40% in the fourth decade. As life-expectancy increases in CF, CF-related diabetes (CFRD) will be diagnosed more frequently in the future [1].

Negative consequences of CFRD include: catabolic metabolism, weight loss, more frequent/more severe infections, deterioration of pulmonary function, reduced life-expectancy and diabetic micro vascular complications [2].

Up to date, insulin is the only recommended treatment of CFRD, whether newly diagnosed or not. But no data are available to answer the question if CFRD must always initially be treated by insulin [3]. Several centres report the successful management of CF-related diabetes using oral anti-diabetic drugs at least for some years [4,5]. Oral therapies would be less invasive for a patient group which is highly traumatized by a very demanding pharmaceutical therapy (including antibiotics, pancreatic enzymes, bronchodilators, mucolytic agents) in addition to physiotherapy. Based on an initiative of the German CF-Foundation (Mukoviszidose e.V.), the present study tries to answer the question, whether oral therapy with repaglinide is as effective as insulin therapy in CF patients with early diagnosed diabetes mellitus.

### Primary objective

The primary objective of this trial is to compare the glycaemic control on oral therapy with repaglinide tid with that on insulin therapy with three daily injections of regular Insulin over 2 years in patients with CF and CFRD.

### Secondary objectives

The secondary objectives of this trial are to compare the two treatment regimen (oral therapy with Repaglinide and insulin therapy with regular insulin) in terms of efficacy and safety.

The efficacy objectives are change in glycaemic control after 12 months of treatment, glycaemic control assessed by glucose profile done monthly (6 values), change in nutritional status and pulmonary function at 12 and 24 months, as well as the need for antibiotic treatments.

The safety objectives are the incidence and quality (mild, severe, other) of hypoglycaemic episodes and adverse events.

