### Trial conduct

In all CF-patients 10 years or older, an oral glucose tolerance test (OGTT) following standard WHO recommendations has be performed. Oral medication was postponed until after the test, however, inhalation therapy could be performed prior to the test. During acute infections or exacerbations of a chronic infection, the test was postponed for 3 to 4 weeks until acute symptoms improved. OGTT were classified as normal glucose tolerance, impaired glucose tolerance/impaired fasting glucose or diabetes mellitus according to the WHO cut off values [6].

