### Randomization

After detailed information by the physicians of the local CF centre, the patient or legal guardian decided to give written informed consent to participate in the study. The trial was open-labelled in order to avoid use of double-dummy technique which would have required an unacceptable increase in the number of injections for the patients. The patients were allocated to the treatment regimen according to a randomisation list generated by a geigy random number table by central fax randomisation. Stratification was conducted according to gender and two age groups (10–15 years, >15 years). Every randomised patient should have been observed for at least 2 years and be included in the final analysis (“intention-to-treat” analysis).

The trial procedures are summarised in the following Table 1.

**Table 1 T1:** Trial procedures

**Visits/months**	**VS**	**V1**	**V2**	**V3**	**V4**	**V5**	**V6**	**V7**	**V8**	**V9**	**End**
		**0**	**3**	**6**	**9**	**12**	**15**	**18**	**21**	**24**	
Informed consent	+										
Selection/exclusion criteria	+										
Randomisation		+									
Inclusion/exclusion criteria		+									
Demographic data	+										
Medical history	+										
Physical examination	+	+	+	+	+	+	+	+	+	+	+
Concomitant illness and medication	+	+	+	+	+	+	+	+	+	+	+
Blood glucose profile			+	+	+	+	+	+	+	+	+
HbA_1c_		+	+	+	+	+	+	+	+	+	+
Pulmonary function		+	+	+	+	+	+	+	+	+	+
IV therapy (antibiotics)		+	+	+	+	+	+	+	+	+	+
Adverse events		+	+	+	+	+	+	+	+	+	+
Hypoglycaemic episodes			+	+	+	+	+	+	+	+	+
Drug dispensation		+	+	+	+	+	+	+	+		

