### Therapy duration

Patients in both therapy strains hade to be monitored for 2 years; every 3 months, a standardised examination and documentation was intended.

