### Reasons for study duration

No relevant short-term changes have been expected among early diagnosed patients, especially concerning weight development and lung function [11]. Evidence of successful diabetes therapy with an oral anti-diabetic stretching over 2 years was planned to show constitute clinically relevant results compared with a shorter duration.

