### Outcome measures

Primary endpoint:

Primary endpoint was the change in HbA1c after 24 months of treatment.

Secondary endpoints:

Secondary endpoints were glycaemic control assessed by mean HbA1C and mean blood glucose profile; change in BMI-Z-score; change in FEV1% predicted and safety assessed by antibiotic therapy, incidence of adverse events, number of hypoglycaemic episodes, all symptomatic hypoglycaemia, hypoglycaemia that necessitates the help of other persons, hypoglycaemia with unconsciousness or coma and number of blood glucose levels below 50 mg/dl in relation to all blood glucose measurements.

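### FEV1 and BMI-Z-score are compared as change at months 12 and 24 by two-sample tests, so most quarterly values and the data of early leavers go unused

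*Protocol article*

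**What the plan says.** Under Secondary objectives the article lists "change in nutritional status and pulmonary function at 12 and 24 months". Outcome measures repeats the endpoints as "change in BMI-Z-score; change in FEV1% predicted and safety assessed by antibiotic therapy" and mentions no slope, average or other use of several visits.

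Power calculation/analysis names the methods. HbA1c gets a repeated-measures ANOVA. Secondary parameters are compared by Fisher's exact test, the Wilcoxon test or the t-test. The same section assumes that about 30% of patients drop out over two years. The Randomization section says that every randomised patient should be observed for at least two years and be part of an intention-to-treat analysis.

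Therapy duration states that "every 3 months, a standardised examination and documentation was intended". In Table 1, the row "Pulmonary function" is marked at V1 to V9 (months 0, 3, ..., 24) and at the End column. Table 1 has no weight, height or BMI row; only "Physical examination" could cover nutritional status at those visits. Reasons for study duration gives the expectation behind the two years: "No relevant short-term changes have been expected among early diagnosed patients, especially concerning weight development and lung function".

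**The concern.** The t-test and the Wilcoxon test take one value per patient. When the endpoint is a change at a named month, that value is most naturally the month's measurement minus baseline. The repeated-measures method is given to HbA1c only, although FEV1 is scheduled at the same visits.

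Two things are at stake. The first is precision: the article itself expects slow change in weight and lung function, and repeated measurement can help to separate a slow trend from visit-to-visit noise. The second is who is analysed: a patient who leaves before month 24 has no month-24 change, so the comparison rests on completers or on an imputed value. That sits badly with the stated intention-to-treat aim. The Abstract names these two outcomes as the secondary endpoints, and the Discussion promises a direct comparison between the groups, so their analysis deserves care.

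**Working it through.** **Figures the article gives.** There is no SD, effect size or power for FEV1 or BMI-Z-score, so there is no figure to reproduce for this point. The only sample-size result concerns HbA1c: difference 1.0, SD 1.5, two-sided 0.05, power 80%. A t-test calculation gives 36.3, hence the stated 37 per group. It says nothing about lung function or nutrition.

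**Visits used.** Scheduled FEV1 values: months 0, 3, 6, 9, 12, 15, 18, 21, 24, nine in all. Needed for change at 12 and 24 months: months 0, 12 and 24. Not used: 9 − 3 = 6.

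**Dropout.** At 30% of the planned 111 patients, 0.30 × 111 ≈ 33 would lack a month-24 value if dropping out means lost to follow-up. A two-sample test of month-24 change cannot include them without imputation. A mixed model uses whatever quarterly values they supplied.

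**Precision, under assumptions.** Let w be the within-patient SD at a visit and b the between-patient SD of the true 24-month change, both in points of FEV1% predicted. Neither is in the article; I take w = 4 to 8 and b = 6 to 10.

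- Two-visit change, independent errors: variance = b² + 2w².
- Least-squares slope over nine visits, times 24 months: the sum of squared deviations of the visit months is 540, so variance = b² + (24²/540)w² = b² + 1.067w².
- Errors with correlation ρ between neighbouring visits and ρ^k at k visits apart: the two-visit factor becomes 2(1 − ρ⁸). The slope factor, by generalised least squares, is 1.512, 1.778 and 1.842 at ρ = 0.3, 0.5 and 0.7. The two-visit factors are 2.000, 1.992 and 1.885. The ratios for error variance alone are 0.53 (ρ = 0), 0.76, 0.89 and 0.98.

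Total variance per patient, two-visit change to nine-visit slope. The rows include the smallest and largest reductions over the assumed ranges:

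| w, b | ρ = 0 | ρ = 0.5 | ρ = 0.7 |
|---|---|---|---|
| 4, 10 | 132 to 117.1 (−11%) | 131.9 to 128.4 (−3%) | 130.2 to 129.5 (−0.5%) |
| 6, 6 | 108 to 74.4 (−31%) | 107.7 to 100.0 (−7%) | 103.8 to 102.3 (−1.5%) |
| 8, 6 | 164 to 104.3 (−36%) | 163.5 to 149.8 (−8%) | 156.6 to 153.9 (−1.7%) |

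These reductions belong to a linear slope fitted to complete data. A model with visit as a category makes no linearity assumption. With complete data it gains little at month 24 over a baseline-adjusted comparison; its benefit comes from patients with incomplete follow-up.

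**The case against.** The strongest reply is that nothing here is contradictory or miscalculated. Collecting quarterly data and reporting at months 12 and 24 are compatible. The article never says that intermediate visits are excluded, and a condensed article may leave secondary models to the full protocol or analysis plan. That the comparison uses single visits is therefore an inference. It stands as the natural reading because the article does name the tests for secondary parameters and does reserve the longitudinal method for HbA1c. This is a stated choice, not a gap.

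It can also be said that the precision gain is uncertain. That is correct: with strongly correlated visit errors it almost disappears. The Table 1 End column might supply a last value for early leavers, but using it as month 24 would itself be an imputation. Patients who only stop study treatment may still be followed, so 30% may overstate the missing values.

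Nine nutritional measurements per patient cannot be read from Table 1; they are only plausible from the physical examination row.

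A reader might go further and infer two things that the article does not support.

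- *That a missing exacerbation rule for spirometry is a flaw.* Trial conduct says of the OGTT that "During acute infections or exacerbations of a chronic infection, the test was postponed for 3 to 4 weeks until acute symptoms improved", and no such rule is printed for FEV1 or weight. Measurement conditions are a detail that a condensed article commonly omits, so silence here does not show absence from the trial. The last patient entered in December 2009 and analysis is under way, so postponing visits is moot. Dropping visits during intravenous antibiotics would condition on a post-randomisation event: the article lists infections among the consequences of the disease and antibiotic therapy among the outcomes.
- *That the trial cannot exclude a relevant harm to FEV1 or BMI.* The article gives no margin and no variance for either outcome, so this cannot be shown.

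**Conclusion.** The point holds as an improvement to a stated secondary analysis, not as an error in a figure or a contradiction. On the natural reading, six of nine scheduled FEV1 values enter neither comparison, and patients without a month-24 value drop out of that comparison unless one is imputed. The second consequence is the firmer one, since it follows from the planned test and the expected dropout and does not need the assumed variances. The precision gain is conditional: about 11% to 36% lower variance of the 24-month change with independent visit errors, about 3% to 8% at autocorrelation 0.5, and under 2% at 0.7. These ranges rest on assumed SDs and on a linear course. For BMI-Z-score the point applies only if weight and height were recorded quarterly.

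**What to change.** Replace the t-test or Wilcoxon comparison of FEV1% predicted with a mixed model on all quarterly visits, containing baseline value, treatment, visit and treatment by visit. Report the treatment difference with its confidence interval at months 12 and 24, which keeps the stated endpoints. Treat BMI-Z-score the same way where weight and height were recorded at the quarterly physical examination. Add a model with linear time and random intercept and slope as a supporting analysis.

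The cost is a change of analysis wording, using data already scheduled for collection; it should be fixed before the treatment groups are compared. The price is modelling assumptions. Missing values must be missing at random given the observed data, which is open to doubt because some discontinuation criteria, such as tube feeding or transplantation, relate to nutrition and lung disease. The slope version also needs a roughly linear course.
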